## Objectives

This study is a randomized, evaluator- and statistician-blinded, parallel-controlled, superiority trial.

The purpose of this trial will be to assess the following:
Whether Tuina combined with Yijinjing is not inferior to Tuina regarding pain, disability, and negative emotions for patients with NCNP

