**Discussion:**

The purpose of this trial is to determine whether Yijinjing combined with Tuina is not inferior to Tuina for patients with NCNP. This study will provide clinicians and stakeholders much-needed knowledge for a complementary and alternative therapy for patients with non-specific chronic neck pain.

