Studies have shown that a single treatment plan is not effective, so the combination therapy has received more attention and is recommended by related scholars [34, 35]. There is quite a little evidence for the efficacy of Tuina on non-specific chronic neck pain, especially when combined with Yijinjing. We hypothesize that Tuina and Yijinjing have beneficial effects on non-specific chronic neck pain because that is a case with subacute and long-lasting neck pain [36]. We want to further explore whether Tuina combined with Yijinjing exercises can play a better role in pain, disability, and negative emotions. Thus, we designed a randomized controlled trial (RCT) to prove our hypothesis. This trial will provide a solid clinical foundation for the efficacy of Yijinjng combined with Tuina. It will be served as a prospective experiment as well.

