### Sample size calculation

The following two hypotheses are related to the differences between the two groups.
H0:μ1 − μ2 ≤ ΔH1:μ1 − μ2 > Δ

where μ1 is the VAS score for treating 8 weeks in the Tuina group, and μ2 is the VAS score for treating 8 weeks in the Tuina combined with Yijinjing group.

According to a previous clinical study in China [53], the mean and standard deviation of VAS in the Tuina group (*n* = 34) after the intervention was 5.5 and 1.1, respectively. The mean and standard deviation of VAS in the Tuina combined with neck exercise group (*n* = 34) after the intervention was 4.7 and 1.3, respectively.

The following formula was used to calculate the sample size in this trial:
$$ n=\frac{2{\left({z}_{\alpha /2}+{z}_{\beta}\right)}^2\times \kern0.5em {\sigma}^2}{{\left({\mu}_2-{\mu}_1-\varDelta \right)}^2} $$

$$ {\displaystyle \begin{array}{l}n=\frac{2{\left(1.96+0.84\right)}^2\times {1.3}^2}{{\left(4.7-5.5-0\right)}^2}=42\\ {}\end{array}} $$

(*α* = 0.05 *β* = 0.2, superiority design, the two-sided test, *Δ* = 0)

Considering a dropout rate of 20%, each group will require 51 cases. Therefore, a total of 102 participants should be recruited for this randomized controlled trial (RCT).

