## Discussion

Non-specific chronic neck pain (NCNP) is a common and high prevalence musculoskeletal problem in the world. It can cause ADL, work disability and economic cost, and psychological stress [54, 55]. Because of the high recurrence rate, a scientific and reasonable intervention should be explored and promoted. It can not only relieve symptoms and reduce the burden of individuals and the society, but also decrease the complication and improve the quality of life. Yijinjing and Tuina are important components of traditional Chinese medicine. They have been used for thousands of years to keep people healthy. Quite a few people know the concrete operating procedure, advantages, and efficacy of such interventions. Therefore, the aim of this study is to investigate whether Yijinjing combined with Tuina has any superiority to Tuina.

According to TCM, a healthy human body depends on the coordination of the internal organs and the harmony of qi and blood. The main reason of pain will be attributed to qi stagnation and blood stasis. In this study, relaxing manipulation, clicking on the acupuncture point manipulation, and neck structural rectification are chosen to release adhesion and smooth joint movement so as to alleviate pain and improve joint movement condition. By using these manipulations, the circulation of qi and blood will be promoted. Five movements of Yijnjing which are specifically for the neck are chosen. These movements include neck flexion, rotation, and lateral flexion. The features of Yijijing are the harmony of body, breath, and mind. It puts emphasis on the unity of strength and meditation by using static postures and dynamic movements. It can circulate qi and blood, strengthen the muscles and nourish the tissues and organs, and also arrest spasm [56]. The previous study demonstrated that regular and long-term training of Yijinjing can raise the skeletal muscle strength and improve motor function and ADL [57, 58]. A clinical research reported that after 6 months, Yijinjing multiple factors of depression and anxiety dropped significantly. It indicated that Yijinjing can improve patients’ mental conditions [59].

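### The stated purpose is non-inferiority, but the design, hypotheses and sample size are for superiority and no margin is given, so a null result could be claimed as meeting the purpose

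*Protocol article*

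**What the plan says.** The protocol article states its purpose in two incompatible ways.

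**Non-inferiority wording**
- Objectives: "Whether Tuina combined with Yijinjing is not inferior to Tuina regarding pain, disability, and negative emotions for patients with NCNP".
- Abstract, Discussion paragraph: "The purpose of this trial is to determine whether Yijinjing combined with Tuina is not inferior to Tuina for patients with NCNP".

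**Superiority wording**
- Objectives, the sentence before the non-inferiority purpose: "This study is a randomized, evaluator- and statistician-blinded, parallel-controlled, superiority trial".
- Introduction, last paragraph: "We want to further explore whether Tuina combined with Yijinjing exercises can play a better role in pain, disability, and negative emotions".
- Sample size calculation: "superiority design, the two-sided test", with Δ = 0. The alternative hypothesis is that mean VAS at 8 weeks is higher under Tuina alone (μ1) than under the combination (μ2).
- Main Discussion: "the aim of this study is to investigate whether Yijinjing combined with Tuina has any superiority to Tuina". A later paragraph of that section again asks whether the combination is the better treatment.

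The Statistical analysis section plans an intention-to-treat analysis at p < 0.05 and counts non-completers as unchanged from baseline. It gives no margin and no rule based on a confidence bound.

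**The concern.** The stated purpose tells readers what the trial may conclude. Superiority asks whether the difference is demonstrably above zero. Non-inferiority asks whether a deficit larger than a margin fixed in advance has been ruled out. Here the abstract and the Objectives section ask the second question, while the only specified test answers the first.

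If the superiority test fails, the published purpose still leaves room to say that the combination was not inferior. Nothing in the document would contradict that claim, because it names no deficit that has to be excluded. The Objectives sentence covers pain, disability and negative emotions, and a margin is missing for all three. The planned 5% error control applies to the superiority test and not to such a claim.

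**Working it through.** **1. Reproduce the plan's sample size.** Inputs from Sample size calculation: means 5.5 (Tuina) and 4.7 (Tuina plus neck exercise), SD 1.3, z-values 1.96 and 0.84, Δ = 0.

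n = 2 × (1.96 + 0.84)² × 1.3² / (4.7 − 5.5 − 0)² = 41.4, rounded up to 42 per group.

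The plan's 51 per group is 42 × 1.2 = 50.4, rounded up, giving 102 in total. The figure reproduces as a superiority calculation with Δ = 0.

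**2. Is Δ = 0 a margin?** Lower VAS is better, so μ1 − μ2 > 0 means less pain with the combination. For non-inferiority, the alternative would be μ1 − μ2 > −m for some positive m. With Δ = 0 the hypotheses are plain superiority.

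**3. Precision.** Half-width of the 95% confidence interval = 1.96 × 1.3 × √(2/n).

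| n per group | Standard error (cm) | Half-width (cm) |
|---|---|---|
| 42 | 0.284 | 0.556 |
| 51 | 0.257 | 0.505 |

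Take the difference as combination minus Tuina, so that positive is worse, with 42 per group:
- An observed difference of 0 gives −0.56 to +0.56. The superiority test fails.
- An observed difference of +0.4 gives 0.4 ± 0.556, or −0.16 to +0.96. This is also non-significant, although the upper limit exceeds the 0.8 cm on which the trial is sized.

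Without a margin, the document gives no ground for treating either result as a failure of its stated purpose.

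**4. How often would a real deficit go unflagged?** Assume for illustration that the combination is truly 0.5 cm worse. The probability of a non-significant two-sided test is Φ(1.96 − 0.5/SE) − Φ(−1.96 − 0.5/SE). This is 0.578 at 42 per group and 0.507 at 51.

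**5. What if non-inferiority were meant?** The required size cannot be derived, because no margin is given. The table uses assumed margins, SD 1.3, true difference 0, one-sided 2.5% and 80% power.

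| Assumed margin (cm) | n per group before dropout | Power at 42 per group |
|---|---|---|
| 0.5 | 107 | 42% |
| 0.8 | 42 | 81% |
| 1.0 | 27 | 94% |
| 1.5 | 12 | over 99% |

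Whether the present size would support a non-inferiority claim therefore depends entirely on a number the document does not contain.

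**6. Missing data.** If dropout and baseline scores are similar in the two arms, counting non-completers as unchanged pulls the arm means together. At the planned 20% dropout, a true deficit of 0.5 cm would shrink to about 0.8 × 0.5 = 0.4 cm. That is conservative for superiority but favours a non-inferiority reading.

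**The case against.** The best reply is that the operative text already settles the matter. The design label, hypotheses, value of Δ and sample size are all superiority, and so are the aims in the Introduction and main Discussion. On this view the two non-inferiority sentences are loose wording, and anyone holding the Sample size section could reject a non-inferiority claim at once. The article nowhere says that a null result will be reported as a success, and the Specific primary objective names neither framework.

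Much of this stands. Superiority is very probably what was intended, and misreporting is a risk inferred from the text, not something the plan announces. The missing margin is what one expects of a superiority trial, so it is not a separate defect. The absence of a per-protocol analysis carries no weight, since an article may leave that to the full protocol or SAP. Using SD 1.3 for both arms follows the plan's formula. Averaging the two quoted variances gives an SD of about 1.20 and half-widths of about 0.51 and 0.47 cm, which changes nothing of substance.

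The reply does not remove the contradiction. The wording appears twice, in the two places where readers look for a trial's purpose, and in Objectives it directly follows the superiority label. A reader should not have to infer the purpose from the sample size formula. The figure of 42 cannot settle the question alone, because the same number would result from non-inferiority with a 0.8 cm margin and no true difference. Only the explicit statements of superiority and Δ = 0 decide it.

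**Conclusion.** The concern holds. The purpose given in the abstract and in Objectives contradicts the trial's only specified hypothesis test, and no margin exists by which a non-inferiority claim could be judged. The contradiction needs no assumptions. The figures for its consequences rest on the plan's SD of 1.3 cm, a normal approximation, and an illustrative true deficit of 0.5 cm, which a non-significant test would miss in roughly half or more of such trials (51% to 58%). The planned superiority test and its sample size are not undermined. What is wrong is the statement of what that test is meant to show, and it should be corrected before results are interpreted.

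**What to change.** In Objectives and in the Discussion paragraph of the abstract, reword the purpose so that it asks whether the combination is superior to Tuina alone. Add one sentence, for example in Statistical analysis: the only confirmatory claim is superiority on VAS at a two-sided 5% level, and a non-significant result will not be interpreted as non-inferiority or equivalence. Date the correction and make it before the data are locked and unblinded. The cost is two rewordings and one added sentence. Patients, visits, sample size and the planned test are unaffected.

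If the sponsor did intend non-inferiority, rewording is not enough. The plan would then need a justified margin for each outcome claimed, a decision rule based on a confidence bound, defined analysis sets, a handling of non-completers that does not favour the claim, and a new sample size calculation.

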### Specific primary objective

The specific primary objective is to determine the change in the visual analog scale (VAS) pain scores from baseline, 4 weeks during the intervention, at the end of the intervention, and 1 month after the intervention within and between the two groups.

### Specific secondary objectives

The specific secondary objectives are to determine the change in scores of Neck Disability Index (NDI), Self-Rating Anxiety Scale (SAS), and Tissue Hardness and Active Range of Motion (AROM) from baseline, 4 weeks during the intervention, at the end of the intervention, and 1 month after the intervention within and between the two groups.

## Methods/design

### Study design

This present study is a single-center, randomized, and analyst-blinded controlled trial with two arms: Tuina group (control) and Yijinjng combined with Tuina group (intervention). The study protocol has been approved by the Regional Ethics Review Committee of Yueyang Hospital of Integrated Traditional Chinese and Western Medicine affiliated with Shanghai University of Traditional Chinese Medicine (project number: 2020-018). A total of 102 eligible NCNP patients will be recruited and assigned in a 1:1 ratio randomly. Written informed consent will be provided by all patients. Independent researchers who are blinded to the patient assignment will collect and analyze the outcome assessment and related data. The study design is illustrated in the flow chart in Fig. 1. The main treatment center will be the Shanghai University of Traditional Chinese Medicine.

**Fig. 1 Fig1:**
[figure not shown]
Trial flow chart. Diagram demonstrating the randomized controlled trial protocol. A total of 102 eligible NCNP patients will be randomly allocated to the group of Tuina and Tuina combined with Yijinjing in a 1:1 ratio. The dropout will be analyzed by ITT analysis

### Participants and recruitment

Eligible participants include patients diagnosed with NCNP according to the base guideline for the chiropractic treatment of adults with neck pain which is summarized by GDC of Canada [37]. Patients with non-specific neck pain for more than 3 months (no relief for more than 2 weeks) for the first time in the Tuina Department of Yueyang Hospital of Integrated Traditional Chinese and Western Medicine affiliated with Shanghai University of Traditional Chinese Medicine will be informed about this trial. If the patient expresses interest in this trial, a clinical trial communicator will make a contract with him/her immediately and make a brief introduction about the trial. If the patient decides to take part in this trial, he/she will have a face-to-face interview in a reception room of the Shanghai University of Traditional Chinese Medicine. Patients who meet the inclusion criteria will join the trial after they sign the informed consent form.

We recruit the potential participants in the following ways:
Posters on affiliated hospitals of Shanghai University of Traditional Chinese Medicine and nearby community centersOn WeChat platforms and microblogBy printing ads on the newspaper

### Inclusion criteria

Participants who meet all the following criteria can be enrolled:
Aged 20–50Individuals from either sexCurrent neck pain (localized to the cervical or bilateral scapular region)Negative sign of neck distraction test, Spurling’s neck compression test, and Adson’s testHave neck pain symptoms of at least 3 months’ durationVisual analog scale (VAS) ≥ 3 and Neck Disability Index (NDI) score ≥ 10 at recruitment timeNo previous shoulder or neck surgery and no accompanying shoulder problemsWillingness to participate

### Exclusion criteria

Participants meeting any of the following criteria will be excluded from this trial:
Specific disorders of the cervical spine, such as disk prolapse, spinal stenosis, postoperative conditions, cervical radiculopathy, or myelopathyHistory of whiplash injury and/or head/neck injuriesAre pregnant or have had a recent deliveryResponse to prior treatment (a patient with neck pain radiating into the arm whose arm pain resolved with an injection or medication)History of severe trauma, spasmodic torticollis, frequent migraine, fibromyalgia, shoulder diseases, inflammatory rheumatic diseases, tumor, osteoporosis, psychiatric illness, and obvious spinal deformity or neurological diseaseNo clinical treatment for neck pain in the past 3 monthsUnable to speak or write Chinese in order to complete the questionnairesAlcohol and drug abuseHave an uncomfortable reaction to TuinaSubjects with regular practice of Yijinjing, Qigong, or Yoga in the past 3 monthsPoor cooperation

### Dropout criteria

Participants who do not complete the clinical protocol for the following reasons should be considered as dropped out:
The patient quits (poor efficacy or adverse reactions)Loss to follow-upResearchers remove the patient (poor compliance or serious adverse events)

### Comprehensive suspension criteria

The trial will be suspended if:
The investigators discover a significant safety problem.The therapeutic effect is poor (we will assess the therapeutic effect at week 4).There is a major mistake in the plan.The sponsor has a huge problem in funding or management.

### Randomization and allocation concealment

The randomization list will be generated by a random number generator (Strategic Applications Software, version 9.1.3; SAS Institute Inc., Cary, NC, USA). The random numbers will be placed in an opaque envelope which has been numbered in order.

Before implementing random assignment, the research team will record the detailed information of each participant in the clinical center, including the new participant (name, date of birth, participant and center code, and date of inclusion) during reporting and preparation of a signed informed consent. The therapist will sequentially open the envelopes and allocate the participants accordingly. Eligible participants will be randomly assigned to the experimental group and the control group according to 1:1 equal proportion rules after the baseline assessment.

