### Blinding

Patients will be informed of the type of treatment that they will receive. The therapists will know the allocation so they should learn how to communicate with patients to ensure treatment blinding. In order to reduce the risk of bias, evaluators, data managers, and statisticians will be unaware of the group assignments in the result evaluation procedures and data analysis. The blinding procedure will be operated until the data are locked.

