### Interventions

The Tuina protocol used in this trial is the same as those used in our previous studies [38, 39]. It includes soft tissue manipulation and spinal manipulation, such as rolling, pressing, and tapping. Yijinjng for NCNP patients was designed on the basis of the textbook which has been used for teaching students in the universities of TCM [40, 41].

Participants in the Tuina group or the Yijinjng combined with Tuina group will receive Tuina treatment 3 times a week for 8 weeks. The treatment room will be controlled at 23–25° to ensure that the participants feel comfortable. The participants will be asked to rest for 15 min before Tuina treatment. They will be advised to lie in the prone position during the treatment. The intensity level of Tuina is based on physical examination and the therapist’s clinical experience, as well as after careful communication with each study participant. Tuina treatment will last for 25 min.

The participants who are in the Yijinjng combined with Tuina group will practice Yijinjing 3 times a week for 8 weeks. The patients will be assembled once a week for practicing Yijinjing together. The Yijinjing teacher will teach them how to practice Yijinjing. The teacher will also correct the wrong movement of patients. The patients will practice Yijnjing another two times per week at home. A digital video disk about the movements of Yijinjing in this trial will be provided to the participants. They can review the movements at home easily. The participants are asked to film themselves and sent it to the teacher by email or WeChat. The teacher will examine the participants’ video carefully and give the patients some advice about practicing Yijinjing. Yijinjing treatment will last for 30 min.

VAS, NDI, SAS, soft tissue hardness, and AROM will be assessed at the baseline and 4, 8, and 12 weeks.

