### Yijinjing combined with Tuina group

In this arm of study, the steps of Tuina treatment are the same as the Tuina group. The Yijinjing teacher will administer a five-step protocol intended to improve the therapeutic effects and adjust physical and mental conditions. The main movements of Yijinjing are shown in Fig. 2.

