### Strengths and limitation of the study

The strength of this trail includes the randomized study design, the pre-defined sample size, and the application of Yijinjing which is designed by an experienced expert. Secondly, the use of standardized measurement instruments will become very important inclusions for the study. Finally, many resistance trainings are limited to equipment-based ones in rehabilitation organizations or hospitals. They cost high and fail to combined positive and passive movement. As a kind of traditional Chinese exercise, it is easy for people to master in a short time. Moreover, Yijinjing does not require expensive equipment. It can not only strengthen the bones and sinews, but also nourish organs. It will make a positive effect on physiological structures and pathological conditions.

There are several limitations to this study. The first is the blinding of the therapist and patients. The nature of the interventions makes it impossible to blind them during the study. Secondly, self-reported results, such as the VAS and SAS, also have limitations because they may be affected by the placebo effect and expected results. Finally, there is in fact no control group. We use Tuina therapy as a control which is considered experimental.

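### A treating therapist opens the randomisation envelopes and so learns the arm, although the Tuina therapist gives both arms the same treatment and need not be told it

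*Protocol article*

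**What the plan says.** All references are to the protocol article.

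- **Randomization and allocation concealment.** On the envelopes: "The random numbers will be placed in an opaque envelope which has been numbered in order". On who uses them: "The therapist will sequentially open the envelopes and allocate the participants accordingly". Allocation is made "according to 1:1 equal proportion rules after the baseline assessment", and the research team records each participant's identifying details beforehand.
- **Blinding.** "Patients will be informed of the type of treatment that they will receive". The next sentence reads: "The therapists will know the allocation so they should learn how to communicate with patients to ensure treatment blinding". Evaluators, data managers and statisticians are to be kept unaware of the groups.
- **Interventions.** Both arms receive Tuina on the same schedule, three sessions a week for 8 weeks. On force: "The intensity level of Tuina is based on physical examination and the" therapist's own experience, together with discussion with the participant.
- **Yijinjing combined with Tuina group.** For this arm, "the steps of Tuina treatment are the same as the Tuina group".
- **Study therapists.** A senior Tuina therapist gives Tuina, and a different person, the Yijinjing teacher, leads the exercise.
- **Strengths and limitation of the study.** On therapists and patients together: "The nature of the interventions makes it impossible to blind them during the study".

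**The concern.** Two separate things are at issue.

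The first is allocation. With an envelope scheme, the usual safeguard is that whoever opens the envelope has no part in treatment. Here the task goes to someone who will treat the participant.

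The second is equality of the shared treatment. The trial estimates what Yijinjing adds to Tuina, and that contrast is clean only if Tuina is delivered alike in both arms. A therapist who knows the arm and has some freedom over intensity could, without intending to, give more effort, attention or encouragement to one group. The primary outcome is a pain score marked by patients who know their own arm, so blinded evaluators cannot remove such an effect. The article presents the therapist's knowledge of the arm as unavoidable, when its own allocation procedure is one source of it.

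**Working it through.** No figure in the article bears directly on this point, so the check is mainly a comparison of its sections.

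**1. Who allocates.** The randomisation section says only that it is the therapist. Under Study therapists, the Tuina provider is called a therapist and the Yijinjing provider a teacher, and the Blinding section confirms that therapists know the allocation. The natural reading is the Tuina therapist. If it were the teacher, a provider would still be allocating.

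**2. Does the Tuina therapist need to know the arm?**

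| Element | Tuina arm | Combined arm |
|---|---|---|
| Tuina steps | three-step protocol | the same |
| Tuina schedule | 3 per week, 8 weeks | the same |
| Tuina session length | 25 min | the same |
| Yijinjing | none | led by the teacher |

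Nothing the Tuina therapist does depends on the arm. The reason given under limitations fits the patients and the Yijinjing teacher, but not the Tuina therapist.

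**3. Exposure.** 3 sessions per week × 8 weeks = 24 Tuina sessions per patient, each with intensity partly left to judgement.

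**4. The Blinding section against itself.** One sentence has patients told their treatment. The next has therapists communicate with those patients so as to ensure treatment blinding. No treatment blinding remains to be protected in patients who have been told.

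**5. Scale, under an assumption.** The size of any bias is not in the documents. The planned difference is 5.5 − 4.7 = 0.8 cm. Suppose there is no true effect, SD 1.3 (the value used in the sample size formula), 51 analysed per group, a normal approximation, and a systematic shift of b cm from unequal Tuina delivery.

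- SE = 1.3 × √(2/51) = 0.257
- Two-sided error rate = 1 − Φ(1.96 − b/SE) + Φ(−1.96 − b/SE)

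| Assumed b (cm) | Error rate |
|---|---|
| 0 | 5.0% |
| 0.1 | 6.75% |
| 0.2 | 12.15% |
| 0.3 | 21.4% |
| 0.5 | 49.3% |

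This shows how sensitive a trial of this size is to a shift, if one occurs. It does not estimate the shift.

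**The case against.** The strongest reply has four parts.

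**Concealment is reasonably protected.** The envelopes are opaque, numbered and opened in sequence. Identifying details and the baseline assessment come first, and a trial communicator, not the therapist, introduces the study. This stands. A reader might infer that the therapist keeps the envelopes and could reorder or anticipate allocations. The article does not support that: it does not state custody, which a condensed article may leave to the full protocol, and it describes nothing that would make the next allocation predictable.

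**Therapist blinding would leak.** Patients know their arm and talk with the therapist about intensity over 24 visits. This also stands. A reader might infer that the Tuina therapist could be kept fully blind; the most the documents support is that the therapist need not be told.

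**Discretion over Tuina is limited.** The soft-tissue and acupoint steps have set durations, 5 + 5 + (5 × 2) = 20 of the 25 minutes. Acupoint force follows the patient's sensation, and providers are trained and tested for consistency. This narrows the room for differences. It does not close it, because overall intensity still rests partly on the therapist's experience.

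**The lack of blinding is disclosed.** It is, but the reason given does not fit the Tuina therapist. Self-reporting by unblinded patients, also disclosed, is a separate limitation that this change would not remove.

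**Conclusion.** The point holds in limited form. A treating person performs the allocation and thereby learns the arm, which weakens concealment without abolishing it. The statement that therapists cannot be blinded is not supported for the Tuina therapist, given the article's own description of identical Tuina and a separate Yijinjing teacher. The two sentences on patients in the Blinding section conflict.

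The size of any resulting bias cannot be computed from the documents. The error rates shown rest wholly on assumed shifts and should not be cited as expected bias, nor as evidence that the trial's result would be wrong. The conclusion also assumes that the therapist who opens the envelopes is one who treats participants, which is how the article uses the word elsewhere. The issue deserves correction because it is avoidable and inexpensive to reduce; it is not fatal to the design.

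**What to change.** - **Randomization and allocation concealment:** have each envelope opened, after the baseline assessment has been recorded, by an existing team member who does not recruit, deliver either intervention, assess outcomes, or manage or analyse data. The Yijinjing teacher would not qualify, being a provider in one arm only. That member informs the patient and, where relevant, the Yijinjing teacher.
- **Blinding:** state that the Tuina therapist is not told the allocation and that patients are asked not to disclose it during Tuina. Delete the clause asking therapists to ensure treatment blinding of patients.
- **Strengths and limitation of the study:** say that only patients and the Yijinjing teacher are necessarily unblinded, and that blinding of the Tuina therapist is expected to be partial.

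The cost is one reassigned task and a short text amendment, with no change to sample size or analysis. There are two downsides. Disclosure by patients over about 24 sessions will leave therapist blinding incomplete. Recruitment has already begun (from May 2020, expected to end in December 2021), so the change applies only to participants not yet allocated. Earlier and later participants will then have been treated under different conditions, and the date of the change should be recorded.
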